## Abstract

**Rationale:**

Cardiovascular exercise is an effective method to improve cardiovascular health outcomes, but also promote neuroplasticity during stroke recovery. Moderate-intensity continuous cardiovascular training (MICT) is an integral part of stroke rehabilitation, yet it may remain a challenge to exercise at sufficiently high intensities to produce beneficial adaptations to neuroplasticity. High-intensity interval training (HIIT) could provide a viable alternative to achieve higher intensities of exercise by using shorter bouts of intense exercise interspersed with periods of recovery.

**Methods and design:**

This is a two-arm, parallel-group multi-site RCT conducted at the Jewish Rehabilitation Hospital (Laval, Québec, Canada) and McMaster University (Hamilton, Ontario, Canada). Eighty participants with chronic stroke will be recruited at both sites and will be randomly allocated into a HIIT or MICT individualized exercise program on a recumbent stepper, 3 days per week for 12 weeks. Outcomes will be assessed at baseline, at 12 weeks post-intervention, and at an 8-week follow-up.

**Outcomes:**

The primary outcome is corticospinal excitability, a neuroplasticity marker in brain motor networks, assessed with transcranial magnetic stimulation (TMS). We will also examine additional markers of neuroplasticity, measures of cardiovascular health, motor function, and psychosocial responses to training.

**Discussion:**

This trial will contribute novel insights into the effectiveness of HIIT to promote neuroplasticity in individuals with chronic stroke.

**Trial registration:**

ClinicalTrials.govNCT03614585. Registered on 3 August 2018

**Supplementary Information:**

The online version contains supplementary material available at 10.1186/s13063-022-06359-w.

## Background and rationale

Exercise training is a recommended core component of comprehensive stroke rehabilitation programs [1, 2]. In the context of stroke, exercise is typically employed on the premise that the brain has a plastic capability (neuroplastic response) to repair itself from neurological damage [3]. A cost-effective method to promote this neuroplasticity is the use of cardiovascular exercise [4]. One bout of exercise performed alone or in concert with non-invasive brain stimulation (e.g., transcranial magnetic stimulation, TMS), may elicit neuroplastic responses that ameliorate motor learning, as studies have demonstrated in healthy individuals [5–7]. Studies in young adults, for instance, demonstrate that cardiovascular exercise can stimulate changes in the excitability of the primary motor cortex (M1) [5–7]. M1 is an important area to target for the promotion of motor function recovery post-stroke [8].

Studies on the acute response to cardiovascular exercise on neuroplasticity in healthy individuals demonstrate that the intensity of the exercise is an integral component in the improvement of neuroplasticity. A single bout of high-intensity interval training (HIIT), a cardiovascular exercise modality that utilizes short periods of high intensities, with interspersed periods of active recovery or rest during the exercise, has demonstrated effectiveness in stimulating neuroplasticity [9, 10] and improving motor learning [11]. Mang et al. reported that 20 min of HIIT at 90% of peak oxygen uptake (VO_2_peak) increased the response to a brain stimulation protocol, amplifying M1 excitability [12]. In contrast, a moderate-intensity continuous (MICT) training protocol (performed at 60% of VO_2_peak) resulted in no benefit to M1 excitability [13].

For individuals with stroke, cardiovascular exercise might also elicit improvement in neuroplasticity and motor recovery [14]. Experiments with animals that have been subjected to a brain lesion have shown that cardiovascular exercise reduces the size of the lesion and inflammation and oxidative stress in perilesional areas [14, 15]. In healthy human subjects, a single bout of HIIT has been demonstrated to be more effective than MICT in stimulating the release of peripheral brain-derived neurotrophic factor (BDNF) [16]. BDNF is a protein that is essential for the promotion of neuroplasticity and motor recovery post-stroke [17, 18]. In young healthy individuals, a single bout of HIIT performed after the practicing of a motor skill can increase BDNF levels, which correlate positively with skill retention, even several days after motor practice [10]. In the context of chronic stroke, acute high-intensity exercise has been described to be associated with larger responses in increased serum BDNF, and additionally greater increases in corticospinal excitability [19, 20].

The importance of higher intensity of exercise is supported by studies which demonstrate the greater improvements in motor learning when motor practice is followed or preceded by a single bout of HIIT, compared to MICT [21]. For instance, studies in individuals with chronic stroke have described that a single bout of MICT may have no effect on M1 excitability, while HIIT can potentially increase affected side excitability, reduce interhemispheric imbalance in excitability, increase neurotrophic factors like BDNF, and improve motor learning [19, 21, 22]. These studies describe a promising methodology of utilizing acute bouts of HIIT exercise; however, eliciting adaptations in brain plasticity that lead to long-term functional recovery (that include functional motor recovery) would require multiple bouts of exercise utilizing a long-term exercise regimen. Therefore, it would be imperative to determine whether multiple bouts of HIIT, in comparison to a MICT program, may result in greater and sustained benefits to neuroplasticity and resultant post-stroke recovery.

### Cardiovascular exercise can improve cardiovascular health for stroke survivors

The most important preventative measure to reduce the risk of stroke is by maintaining ideal cardiovascular health [2, 23, 24]. However, among stroke survivors, cardiovascular comorbidities are highly prevalent. For example, heart disease and hypertension are present in almost 75% and 84% of this population, respectively [25, 26]. Exercise interventions that utilize cardiovascular exercise have been demonstrated to improve cardiovascular risk factors in individuals with stroke such as blood pressure (BP), an important risk factor for primary and secondary stroke [27, 28]. The challenge, however, is that individuals with stroke may be highly sedentary and likely not engage in activities or sustain levels of activity that reduce cardiovascular risk.

Our research group has demonstrated the use of conventional MICT is a safe and feasible method to improve mobility and cardiovascular fitness after stroke [29, 30]. However, like neuroplasticity and motor learning, the intensity of the exercise is a critical component for improving upon cardiovascular health. Our research group has reported greater benefit to cardiac function after 6 months of MICT, when compared to low-intensity exercise [31]. Also observed were improvements in resting BP, among other risk factors, which are only attained when exercise is performed at higher intensities [32].

In order to attain higher intensities of exercise and subsequent benefit to cardiovascular health, HIIT could be a more efficient method than MICT, despite lower amounts of exercise volume. In young adults, for example, 6–12 weeks of HIIT, consisting of short (10–20 min) sessions, performed 3 times per week has been reported to be more effective in improving arterial stiffness, a measure of myocardial demand and coronary perfusion associated with the occurrence of stroke and other cardiac events [33, 34]. A previous meta-analysis has demonstrated that HIIT has resulted in almost a twofold improvement of VO_2_peak compared to MICT [35]. Indeed, HIIT has also been reported to be as or even more effective than MICT in reducing BP [36], for individuals with high BP, despite 20–30% less time devoted to exercise. HIIT could help individuals achieve high intensities that could result in the benefits to cardiovascular health in people post-stroke, which MICT cannot provide. However, a long-term comparison of HIIT vs. MICT for post-stroke individuals has yet to be conducted in a controlled exercise intervention study, in order to fully appraise the extent to which HIIT can yield greater benefit.

### Psychosocial responses to high-intensity exercise are unknown in stroke rehabilitation

While HIIT may provide significant benefits for those with chronic stroke, the adherence to such a physical activity regimen like a HIIT exercise program will depend on several factors such as lack of time [37] and psychosocial determinants such as level of enjoyment [38] and motivation [39]. HIIT may be able to address the prior, as the shorter time commitment has been reported, in healthy populations, as a factor in preference for HIIT in comparison to MICT [40]. Determinants such as enjoyment have been described to be at higher levels in response to HIIT, or similar in comparison to MICT [40–42].

Considering that in the stroke population, the intensities that are achieved may be psychologically demanding, due to heightened cardiovascular and neuromotor effort, it is surprising that an examination of psychosocial factors in HIIT or MICT training for the stroke population is not currently available. An understanding of psychosocial indicators of exercise, like enjoyment and motivation, and how HIIT may affect such outcomes, would provide important information about the potential sustainability of HIIT and its applicability in stroke rehabilitation.

### Objectives

The primary objective of this study is to compare the effects of 12 weeks of HIIT vs. MICT on neuroplasticity. Changes in neuroplasticity will be determined by examining different markers of excitability in upper limb representational areas of M1 with TMS. In addition, the secondary objectives of this study are to compare the effects of HIIT and MICT on measures of cardiovascular health, motor function, and psychosocial responses to exercise. Change in cardiovascular health will be measured by assessing resting BP, arterial stiffness, cardiorespiratory fitness (VO_2_peak), and waist-hip ratio. Psychosocial responses to exercise will examine the effect of HIIT vs. MICT on motivation and enjoyment in response to the respective exercise intervention. Motor function parameters of gait speed, walking capacity, and upper limb motor learning will also be assessed. The exercise interventions of HIIT and MICT will be conducted using a whole-body paradigm, utilizing recumbent steppers.

### Hypotheses

We hypothesize that HIIT will be more effective in promoting neuroplasticity. HIIT will increase the excitability of upper limb representational areas on M1 of the lesioned hemisphere. This will lead to a reduction in the imbalances in M1 excitability that is typically observed in chronic stroke [43, 44]. Based on previous findings [22], we will also expect that the increases in M1 excitability in the lesioned hemisphere after HIIT will be partially mediated by a reduction in intracortical inhibition [45], which is a marker that has been described to increase post-stroke, negatively affecting recovery [8]. HIIT is also expected to be more effective in improving cardiovascular measures of resting BP, arterial stiffness, and VO_2_peak [32, 35]. We predict that after a period of 8 weeks post-termination of the training program (T2), these improvements in neuroplasticity and cardiovascular health will be maintained after to a greater extent in the HIIT group, in comparison to the participants in the MICT group.

We also anticipate greater improvement in walking speed [46], and motor learning post-HIIT, due to an increase in neuromuscular recruitment due to high-intensity exercise, and the aforementioned changes in neuroplasticity, respectively [22]. In contrast, we will also expect a similar improvement in walking capacity in response to either HIIT or MICT. Additionally, responses of motivation and enjoyment will be similar in both groups.

## Methods

The following sections describe the current study protocol (version 1.0 — Dec 2021). This study protocol is presented in accordance with the Standard Protocol Items: Recommendations for Interventional Trials (SPIRIT) guidelines [47].

**Fig. 1 Fig1:**
[figure not shown]
Study flow diagram

### Sites

This study will be conducted at the Jewish Rehabilitation Hospital (Laval, Québec, Canada) and McMaster University (Hamilton, Ontario, Canada).

### Participant eligibility

Participants will be recruited from the Jewish Rehabilitation Hospital (JRH) and Ontario Central South Stroke Network (Hamilton, ON). We will recruit individuals who are in the chronic phase of stroke, which will allow us to test whether HIIT can promote neuroplasticity at later stages in recovery, where changes in neuroplasticity are potentially more difficult to achieve [3]. By recruiting individuals in the chronic stage of stroke recovery, we will also reduce the inter-individual differences in brain excitability, that are observable in the subacute stage of stroke recovery. Participants will be contacted by telephone and screened for eligibility via a screening questionnaire addressing the following inclusion/exclusion criteria:

#### Inclusion criteria

Inclusion criteria include 40–80 years old; 6–60 months following first-ever, single stroke confirmed by MRI/CT; living in the community and able to independently ambulate at least 10 m (the use of assistive devices is permitted, as many individuals who do regain some ability to walk following stroke do so with some adaptation); and the ability to follow instructions in exercise and assessments. If individuals have communicative difficulty due to speech or language deficits (e.g., aphasia), admission into the study is to be done on a case-by-case basis based on judgment taken by the research group.

#### Exclusion criteria

Exclusion criteria include significant disability, as determined by a modified Rankin scale score of > 2; actively engaged in stroke rehabilitation services or a structured exercise program in addition to the one provided by this study; class C or D American Heart Association Risk Criteria [48]; other neurological or musculoskeletal comorbidities that will prevent safe exercise participation; pain that is made worse with exercise; cognitive, communication, or behavioral issues that may limit safe participation in the exercise program; and contraindications to TMS [49].

Informed consent to participate in the study, prior to entry, will be obtained from the participant by study coordinators, LR and KM, at JRH and McMaster sites, respectively.

### Recruitment strategy

At the JRH site, participants will be admitted from clinician referrals and access to participant databanks from patients who have consented to be contacted for participation in research projects. The JRH stroke program admits approximately 190 patients per year and currently conducts a cardiovascular exercise program that will allow us to recruit individuals who have the most interest in exercise and will meet the inclusion criteria of our stroke study, like those conducted previously in at this site [22].

At the McMaster site, the Ontario Central South Regional Stroke Network and the Regional Rehabilitation Centre at Hamilton Health Science can provide access to the potential 600 new patients with stroke admitted per year. The Regional Rehabilitation Centre will serve as the primary source of recruitment for this site. The McMaster site has already utilized successful strategies for the recruitment of such participants for large community-based exercise trials through these networks.

### Randomization

The unit of randomization will be the participant. The randomization process will use a computer-generated group assignment (http://www.randomizer.org) with a 1:1 allocation ratio into either HIIT or MICT training groups. Participants will be stratified between both sites (JRH and McMaster), and we will conduct the randomization with a variable block size unknown to each site. PIs MR and AT will conduct and conceal the allocation of their counterpart’s site (MR for McMaster, AT for JRH). Upon obtainment of participant consent and completion of baseline assessments (T0), group allocation will be revealed to the participant and assessor.

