### Sample size estimation

Based on previous data [21] and using a linear mixed model, we estimated that we would require 32 participants per group (*n* = 64 total) to detect a 5% increase at T1 in the resting MEP amplitude and intracortical inhibition of the affected hemisphere’s M1 in the HIIT group. An increase of 5% is associated with improved motor function in stroke [2]; therefore, we will consider this difference between HIIT and MICT groups to be clinically significant. The statistical package G*Power was used to determine the sample size required to obtain a power of 80% (alpha < 0.05). We have increased the sample size to 40 per group (*n*=80 total) to accommodate for a 20% attrition rate.

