### Statistical analysis

Estimates of the effect of HIIT and MICT at the end of the intervention (T1) for all outcomes will be determined using linear mixed models. Baseline scores (at T0), age, and sex will be included as covariates for sub-analysis. The primary analysis focuses on T1, but T2 will also be included in the model (except for enjoyment, which will not be measured at T2) to increase the statistical efficiency of the estimate. If group interaction effects are significant, *t*-tests based on the linear mixed models will be employed as planned pairwise comparisons to determine differences between HIIT and MICT. Sex-based subgroup analyses will also be performed for exploratory purposes.

Participant data will be analyzed based on intention-to-treat; therefore, linear mixed models will be the preferred method of analysis as it is more flexible than the analysis of variance, and allows for the correlation of repeated measures within subjects and missing data, as long as missing data are missing at random [85]. Interactions between changes between primary and secondary outcomes will be explored with the Freedman-Schatzkin test, which allows for the identification of mediators of change in small-scale exercise studies [86].

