The design of this study does have several limitations. Firstly, there are limitations in the blinding of subjects and assessors. As mentioned previously, due to a lack of resources, staffing availability has made it not possible to blind assessors and exercise instructors from group assignment. Therefore, we are also unable to blind assessors who have conducted assessments at baseline, T0, and T2.

Secondly, the implementation of HIIT or MICT itself may influence psychosocial responses of enjoyment and motivation. Exercise instructors may require more interaction with participants in the HIIT group, because of the frequent change in intensity level and opportunity for feedback and use of encouragement. This may not occur to the same extent in the MICT group due to the continuous level of intensity. Our research group has implemented several methods, including standardized feedback across both groups to limit these potential effects of HIIT and MICT exercise instruction.

As a multicenter study, this setting may lead to potential inconsistencies between sites with respect to outcome assessments and exercise instruction. This necessitates that there is careful monitoring and standardization of assessment techniques and exercise instruction. Our research group, and our Steering committee in particular, will coordinate training sessions, to implement proper assessment techniques and standardization in both study sites, and regular meetings to maintain adherence to standard operating procedures.

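### Allocation is stratified by site but no site term is named for the mixed models; if site is prognostic, standard errors will be somewhat too large and some power lost

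*Protocol article*

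**What the plan says.** The Randomization section of the protocol article allocates individual participants "with a 1:1 allocation ratio into either HIIT or MICT training groups", with variable block sizes, and makes site the only stratification factor: "Participants will be stratified between both sites (JRH and McMaster".

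The Statistical analysis section says that effects at T1 "for all outcomes will be determined using linear mixed models", with T2 also in the model. Its one sentence on covariates reads "Baseline scores (at T0), age, and sex will be included as covariates for sub-analysis". Neither this section nor any other part of the article names site as a fixed or random effect.

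The limitations in the Discussion acknowledge that "this setting may lead to potential inconsistencies between sites with respect to outcome assessments and exercise instruction". The response given there is training, standardised procedures and regular meetings; adjustment in the analysis is not mentioned.

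Under Sample size estimation the article says "we would require 32 participants per group" for 80% power, the target being "to detect a 5% increase at T1 in the resting MEP amplitude and intracortical inhibition". This is raised to 40 per group for 20% attrition. No SD or within-subject correlation is given.

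**The concern.** Blocking within site balances the arms at each site, so a level difference between sites contributes almost nothing to the true sampling variance of the arm difference. A model that omits site still counts that difference as residual variance. The reported standard error then exceeds the true one, confidence intervals are too wide and tests reject too seldom under the null. The precision that stratification provides is not used.

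The article gives some reason to think that site could matter. Beyond the possible inconsistencies named in the Discussion, the Recruitment strategy section describes different sources: referrals, databanks and an existing exercise programme at one site, a regional stroke network and rehabilitation centre at the other. The sample size has no slack beyond attrition, and the same modelling approach covers all outcomes, so the omission would carry through to the secondary outcomes.

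**Working it through.** **The plan's own figure.** 64 / (1 − 0.20) = 80, so the attrition step reproduces. The 32 per group cannot be reproduced without an SD. Assuming a two-sided 5% test, it implies a standardised effect of (1.96 + 0.84) × √(2/32) ≈ 0.70 (0.71 with the t distribution). That is an SD of about 7.0 to 7.1 percentage points for a 5-point difference.

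**Inputs.** From the article: two sites, 1:1 blocked allocation within site, 64 evaluable participants, 80% power, alpha 0.05. Assumed, because the article does not give it: R², the share of outcome variance explained by site, set at 5%, 10% and 20%.

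**Case A: no baseline adjustment.** Take the within-site SD as the one that gives 80% power, so the standardised signal is 1.96 + 0.84 = 2.80.

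- Overstatement of the standard error: f = 1/√(1 − R²)
- Actual type I error of a nominal 5% test: 2 × [1 − Φ(1.96 f)]
- Power: 1 − Φ(1.96 f − 2.80)

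| Site R² | f | Type I error | Power |
|---|---|---|---|
| 0% | 1.000 | 5.0% | 80% |
| 5% | 1.026 | 4.4% | 78.5% |
| 10% | 1.054 | 3.9% | 76.9% |
| 20% | 1.118 | 2.8% | 72.9% |

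A simulation of a single T1 comparison (20,000 trials per setting, n = 64, exact balance within site) agrees. Without a site term, at R² of 5%, 10% and 20%, the ratio of reported standard errors (site omitted to site included) was 1.03, 1.06 and 1.12, type I error 4.4%, 3.8% and 3.0%, and power 78.2%, 77.4% and 72.7%. At R² of 1%, power was 79.7%. With site in the model, power stayed at about 80% and type I error at about 5%. A 25:75 split between sites gave nearly the same values.

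**Case B: baseline score in the model.** Assume the same site shift at T0 and T1, within-site variance 1 at both times and within-site correlation ρ (0.5 to 0.7, not in the article). Let v = R²/(1 − R²) be the site variance. The residual variance given baseline is

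- without site: (1 + v) − (ρ + v)²/(1 + v)
- with site: 1 − ρ²

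The square root of their ratio compares the reported standard error without site to that with site.

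| Site R² (v) | ρ | Without site | With site | Ratio of SEs |
|---|---|---|---|---|
| 10% (0.111) | 0.5 | 0.775 | 0.750 | 1.017 |
| 10% (0.111) | 0.7 | 0.519 | 0.510 | 1.009 |
| 20% (0.25) | 0.5 | 0.800 | 0.750 | 1.033 |
| 20% (0.25) | 0.7 | 0.528 | 0.510 | 1.017 |

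Baseline already carries most of a persistent site difference. At R² of 20%, power is then about 78% to 79%, against 72.9% in Case A.

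**Choice of SD.** If the planned 80% rested on a total SD that already contains site variation, omitting site leaves planned power intact and adding it is a gain: to about 82%, 84% and 88% at R² of 5%, 10% and 20%, without baseline adjustment.

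**The case against.** The strongest objection is that this argues from silence. A condensed article need not list every model term, and a fuller plan may contain site. The covariate sentence is tied to a sub-analysis, so it does not claim to be the full list for the primary model. A reader might infer that the plan has decided to exclude site; the article does not say so. What remains is that the article chose to name covariates, including two that are not stratification factors, and left out the one factor that is. Followed as written, its models have no site term.

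The size is also open to challenge. The Case A figures assume no baseline adjustment, and Case B shows how far they shrink with it. The Discussion says that inconsistencies may arise, not that they are expected, and it describes measures to limit them. For the primary outcome, normalising MEP amplitude to muscle contractility and stimulating at 120% of the individual's resting motor threshold may narrow site differences further. These points stand: the loss could be very small.

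A reader might also infer that ignoring a stratification factor biases the comparison or raises the false-positive rate. The documents do not support that. With 1:1 allocation blocked within site the estimate is unbiased, and the error is in the conservative direction.

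**Conclusion.** The point holds as a conditional one about efficiency and calibration. If site is prognostic, models without a site term will report standard errors that are somewhat too large.

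- Without baseline adjustment, the overstatement is about 2.6%, 5.4% and 11.8% at assumed site shares of 5%, 10% and 20%. Power is about 78.5%, 77% and 73%, provided the planned 80% used a within-site SD.
- With baseline in the model, it is about 1% to 3% at site shares of 10% to 20%, under a persistent site shift and within-site correlation of 0.5 to 0.7.
- If site is not prognostic, it is nil.

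The omission and the direction are clear from the text; the size is not, because the article gives neither the site variance nor the SD. It would be too strong to say that power will be lost or that the trial's inference is unsound.

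**What to change.** State in the Statistical analysis section that site (JRH, McMaster) enters as a fixed effect in every between-arm linear mixed model, primary and secondary. A fixed effect suits two sites, since two levels are too few to estimate a site variance well. The cost is 1 degree of freedom and one phrase in the model statement. No new data are needed. If a fuller analysis plan already includes site, the article need only say so.
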